## Abstract

**Introduction::**

Schizophrenia is one of the most severe mental disorders with a prevalence of about 1% and a leading cause of disability among young adults. Pharmacotherapy is the mainstay in the management of schizophrenia. However, even with the best of medication, several problems like refractoriness, negative symptoms, frequent relapses, and cognitive impairments persist.

**Methods::**

This is a randomized-controlled clinical study including patients from an urban tertiary hospital and a semi-urban community center, with a between-group, repeated-measures, longitudinal design. This study will recruit 160 patients with DSM 5 diagnosis of schizophrenia who are on stable medication for a minimum of 6 weeks; they will be randomly assigned into 2 arms viz., yoga therapy (YT), and treatment-as-usual (TAU) with 80 patients in each arm. Participants will undergo Clinical, Laboratory, and Radiological assessments at baseline and at intervals of 1 month, 3 months, and 6 months from the baseline. It is hypothesized that yoga will improve psychopathology and emotion processing, increase serum brain derived neurotrophic factor (BDNF) and plasma oxytocin levels and effect changes in cerebral activation in areas of the brain associated with schizophrenia.

**Discussion::**

This study aims to measure the efficacy of a Yoga-based intervention as an adjunct in patients with schizophrenia as well as the mechanisms of these effects.

**Trial registration:** Registered retrospectively with Clinical Trial Registry – India (CTRI) with registration number CTRI/2017/08/009219.

## Introduction

1

Schizophrenia is a severe mental illness with a tendency to have a chronic course. Antipsychotic medication is the standard treatment, but has its own limitations, especially with negative and cognitive symptoms showing little or no response to antipsychotics. Also, while the classical antipsychotics had limitations of disabling side effects like extra pyramidal side effects (EPS) and tardive dyskinesia, the newer generation drugs have varied metabolic side effects which may in turn worsen the overall well-being. Also, currently there is a significant drug deadlock in schizophrenia.^[1]^ Hence there is a continuous quest for additional modalities of treatment which can alleviate the impairment caused by the illness.

Yoga which is a part of the ancient heritage of India has been shown to have significant positive effects in stress, cognitive functioning, and neuropsychiatric disorders such as anxiety and depression.^[2–4]^ Yoga and pranayama also have demonstrated efficacy in reducing metabolic parameters such as cortisol in stress-related disorders, serum insulin, and lipid profile in metabolic disorders.^[5,6]^

There is also recent evidence showing that yoga facilitates neuroplasticity in disorders such as depression^[7]^ and that yoga can increase neurotransmitter levels in certain brain regions.^[8,9]^ Preliminary studies also show that yoga and meditative practices may increase cortical thickness,^[10]^ and increase volume of grey matter in parts of the brain important for memory and cognition.^[11,12]^ Thus, yoga based interventions have the potential to ameliorate the residual symptoms in schizophrenia and adaptively modulate the neuroplasticity abnormalities in this disorder.

### Yoga in schizophrenia

1.1

Yoga-based intervention has been shown to significantly improve clinical symptoms and functioning in patients with schizophrenia.^[13,14]^ We have developed and validated a specific module of yoga for schizophrenia^[15]^ and demonstrated significant improvement in symptoms (particularly negative symptoms and emotion recognition deficits) as well as real-life functioning.^[16–18]^ It is noteworthy that some of this clinical work has been recognized by the expert panel of National Institute of Health and Care Excellence (NICE) (UK) in the 2014 guidelines for Schizophrenia as “high quality” evidence for use of yoga in schizophrenia, leading to a recommendation for the use of yoga as a complementary treatment in schizophrenia for the first time.

In a study on stable patients with schizophrenia, it was found that serum oxytocin levels rose after the practice of yoga along with improvement in clinical symptoms.^[19]^ However, this is preliminary, and more research needs to be done to systematically elucidate the effects of yoga in schizophrenia, the biological mechanisms involved, and the role of neuroplasticity. The recent NICE guidelines also called for more systematic research into the effects of physical therapies such as yoga in psychosis.

To summarize, there are many promising leads that support the utility of yoga-based interventions as an important add-on option for treating schizophrenia patients; a comprehensive evaluation of clinical benefits with concurrent evaluation of its potential neurobiological correlates will further strengthen the translational implications of yoga in schizophrenia. The proposed study is an attempt to fill the knowledge gap in this area. Our previous studies (including waitlist and physical exercise arms) have shown the efficacy of add-on yoga therapy for patients with schizophrenia. The current study is aimed at replicating the clinical results as well as examining the biological mechanisms involved.

### Objectives

1.2

#### Primary objectives

1.2.1

1.To systematically assess the effect of yoga-based intervention as an add-on treatment in schizophrenia on psychopathology and social cognition using a randomized controlled design.2.To investigate the neurobiological mechanisms of action of yoga in schizophrenia by assessing serum brain derived neurotrophic factor (BDNF), plasma oxytocin and functional magnetic resonance imaging (fMRI).

#### Secondary objectives

1.2.2

1.To assess the effect of yoga-based intervention as an add-on treatment in schizophrenia on quality of life, perceived stress levels, and socio-occupational functioning.2.To investigate the effects of yoga-based intervention on serum cortisol, serum insulin like growth factor-1 (IGF-1), expression of BDNF and oxytocin gene in peripheral lymphocytes in patients with schizophrenia.

### Hypotheses

1.3

#### Primary hypotheses

1.3.1

In patients with schizophrenia, add-on yoga-based intervention will lead to:

1.Improvement in psychopathology and emotion processing in patients with schizophrenia.2.Increase in serum BDNF and plasma oxytocin levels in patients with schizophrenia.3.Changes in cerebral activation in areas of the brain associated with symptoms of schizophrenia (limbic area and prefrontal cortex).

#### Secondary hypotheses

1.3.2

In patients with schizophrenia, add-on yoga-based intervention will lead to:

1.Improvement in quality of life, perceived stress levels, and socio-occupational functioning in patients with schizophrenia.2.Decrease in serum cortisol, increase in serum IGF-1, and significantly enhanced expression of BDNF and oxytocin gene in peripheral lymphocytes.

## Materials and methods

2

The initial study protocol proposed to randomize patients with schizophrenia on stabilized medication into 3 arms—one with yoga as an add-on intervention, a second arm with a module of physical exercise as an add-on intervention, and a waitlist arm with no additional intervention. However, a pilot phase found that there were significant difficulties in patient acceptance for the exercise arm leading to refusal of randomization in several subjects. Therefore, the protocol was modified in consultation with the funding agency and the Trial Advisory Committee to a two-arm study with the physical exercise arm being dropped. In addition, a community recruitment center was added (District Mental Health Services, Ramanagara, Karnataka, India). Institutional Ethics Committee approval was then obtained for the revised study. The above modification has been communicated to the Trial Registry where the study is registered (Clinical Trial Registry—India).

The source of patients is the outpatient and inpatient services run by the Department of Psychiatry, National Institute of Mental Health and Neurosciences (NIMHANS), Bengaluru, India and the District Mental Health Services, Ramanagara, Karnataka.

### Selection of subjects

2.1

#### Inclusion criteria

2.1.1

(1)Diagnosis of schizophrenia (DSM—V).(2)Clinical Global Impression–Severity^[20]^ (CGI-S) Score ≥3.(3)Age range: 18 to 45 years.(4)Both sexes.(5)Written informed consent.

#### Exclusion criteria

2.1.2

(1)Risk of harm to self (e.g., suicidal risk) or others (e.g., aggression).(2)Need for electroconvulsive therapy.(3)Subjects who are already practicing/recent practice of yoga/meditation.(4)Comorbid substance dependence in the past 6 months or substance abuse in the past 1 month as per DSM-V, except nicotine.(5)Significant neurological disorder including seizure disorder or recent head injury.(6)Family history of neurological disorder that may complicate diagnosis (for example Huntington chorea).(7)Pregnancy or postpartum (<6 weeks after delivery).

### Clinical assessment

2.2

The demographic and clinical information is collected using structured scales and proforma. Diagnosis of schizophrenia is made as per Diagnostic and Statistical Manual of Mental Disorders^[21]^ (DSM-5) criteria and Mini-International Neuro psychiatric Interview Plus^[22]^ (M.I.N.I.). The clinical diagnosis is confirmed independently by a qualified psychiatrist. Psychopathology is assessed using the Scale for Assessment of Positive Symptoms^[23]^ (SAPS); Scale for Assessment of Negative Symptoms (SANS),^[23]^ and Brief Psychiatric Rating Scale (BPRS).^[24]^ Social cognition is assessed by the Tool for Recognition of Emotions in Neuropsychiatric disorders^[25]^ (TRENDS). Social and occupational performance is rated on the Social Occupational Functioning Scale^[26]^ (SOFS) and Quality of life on the World Health Organization's quality of life assessment^[27]^ (WHOQUOL-BREF). Perceived stress is rated using the Cohen Perceived Stress Scale.^[28]^ Adverse effects of antipsychotics are assessed using the Simpson Angus Scale for Extrapyramidal Symptoms^[29]^ (SAS) and the Abnormal Involuntary Movements Scale (AIMS).^[30]^

#### Sample size estimation

2.2.1

For evaluating the primary objectives, the optimal sample size was estimated using the principles and methods^[31]^ for the assessment of primary parameters (SAPS, SANS, and BPRS scores, serum BDNF, Oxytocin, TRENDS fMRI). Based on approximation and estimation from the previous data on the clinical effects of add-on yoga therapy on these parameters in schizophrenia patients^[7,16,18]^ supporting a medium effect size for yoga-based intervention, it was estimated that, for an allocation ratio of 1, a sample size of at least 67 schizophrenia patients in each arm for the pre- versus post- comparisons of patients will be required to detect a two-tailed significant difference of *α* = 0.01 with an estimated 90% power. The study plans to recruit 80 patients in each arm (a total of 160 patients) to account for potential drop-outs.

The subset sample size of 50 in each arm for imaging studies (in each group—pre as well post brain scans) is sufficient to perform random effect analysis for fMRI BOLD changes with multiple comparison correction using random field theory based family-wise error correction to control for multiple comparison (http://www.fil.ion.ucl.ac.uk/spm/).

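### The 90% power is stated for pre-versus-post comparisons with an unquantified medium effect, so it is not demonstrated for the randomised yoga-versus-TAU comparison

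*Protocol article*

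**What the plan says.** Section 2.2.1 (Sample size estimation) presents its calculation as serving the primary objectives. The effect size is described only as "supporting a medium effect size for yoga-based intervention", taken from earlier studies. The other inputs are "for an allocation ratio of 1", a two-tailed test and alpha of "0.01 with an estimated 90% power". The result is that "a sample size of at least 67 schizophrenia patients in each arm for the pre- versus post- comparisons of patients will be required". Recruitment is then set at 80 per arm, 160 in total, to allow for drop-outs. No numeric effect size, standard deviation or baseline/follow-up correlation is given.

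The rest of the article describes a different comparison. The Abstract (Methods) describes a study "with a between-group, repeated-measures, longitudinal design", with follow-up at 1, 3 and 6 months. The first primary objective (section 1.2.1) is to assess add-on yoga "using a randomized controlled design". Section 2.3 randomises 1:1. Section 2.4 defines most primary outcomes as changes in scores or levels, and plans a mixed model without naming the contrast that will be tested.

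**The concern.** A change from baseline within the yoga arm mixes any effect of yoga with time, regression to the mean and continued medication. Only the difference in change between the randomised arms isolates yoga. As worded, the sole power statement for the clinical and laboratory outcomes belongs to the first kind of comparison, while the primary objective needs the second.

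For the same standardised effect, an unadjusted two-arm test needs about twice as many patients per arm as a paired test needs in total, so the difference is not cosmetic. Readers will take the 90% as applying to yoga versus TAU, and a null result could then be over-read as strong evidence of no effect. Section 2.4 also lists baseline-versus-follow-up comparison among the treatment effects in the primary imaging outcome, so the wording in section 2.2.1 does not stand alone.

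**Working it through.** **Inputs from section 2.2.1:** two-sided alpha 0.01, power 90%, allocation 1:1, 67 evaluable and 80 recruited per arm (implied loss 1 − 67/80 = 16.25%).

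**Assumed, because the article gives no figure:** medium is d = 0.5; correlation between baseline and follow-up 0.3 to 0.7.

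**1. The plan's own figure as a pre/post comparison.** Normal approximation: n = (z₀.₉₉₅ + z₀.₉₀)² / d² = 14.88 / 0.25 = 59.5, so 60. The exact paired t-test needs 63, and with 67 patients its power is 92.1%. A Wilcoxon signed-rank test needs 63 / 0.955 = 66. A paired t-test needs about 67 when d is about 0.48. So 67 is near the pre/post answer, but the plain paired t-test at d = 0.5 does not give it exactly.

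**2. Two-arm comparison of change at one time point, unadjusted, d in SD-of-change units.** Normal approximation: n per arm = 2 × 14.88 / 0.25 = 119.04, so 120. The exact two-sample t-test needs 121. Exact power at two-sided alpha 0.01 (noncentrality d√(n/2)):

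| d | 67 per arm | 80 per arm |
|---|---|---|
| 0.4 | 39% | 47% |
| 0.5 | 61% | 71% |
| 0.6 | 80% | 88% |
| 0.7 | 92% | 96% |

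The d detectable with 90% power is about 0.67 with 67 per arm and 0.62 with 80. At alpha 0.05 and d = 0.5, power is 82% and 88%.

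**3. Baseline-adjusted comparison at one visit, d = 0.5 in raw-score SD units.** The effective d is 0.5 / √(1 − ρ²):

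| ρ | Effective d | Power, 67 per arm | Power, 80 per arm |
|---|---|---|---|
| 0.3 | 0.524 | 66% | 76% |
| 0.5 | 0.577 | 77% (76.5%) | 85% |
| 0.7 | 0.700 | 92% | 96% |

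**4. Baseline-adjusted contrast averaged over the three follow-ups.** Assume a constant effect of 0.5 raw-score SD at every visit and equal correlation ρ between all visits. The variance factor is (1 + 2ρ)/3 − ρ². At ρ = 0.5 this is 0.667 − 0.25 = 0.417, so the effective d is 0.5 / √0.417 = 0.775 and power with 67 per arm is about 97%. At ρ = 0.3 it is about 96%.

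**5. Between-arm routes to 67.** An unadjusted two-arm test needs about 67 per arm when d is about 0.67. A baseline-adjusted test at d = 0.5 needs 68 when ρ = 0.67. A change-score test with d = 0.5 in raw-score SD units needs about 67 when ρ is about 0.72 (normal approximation).

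**The case against.** The strongest reply is that the paragraph may describe a two-group calculation loosely. An allocation ratio is an input to a two-group formula and is not needed for a paired test in one arm. Pre-versus-post could mean a comparison between arms of pre-to-post change, which is how section 2.4 defines most primary outcomes. The planned analysis is a mixed model on repeated measures, not an unadjusted test at one visit, and steps 3 and 4 show that such an analysis can reach 90%. An article may also leave calculation details to the full protocol.

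Much of this stands. A reader might infer that 67 can come only from a within-arm test, or that the trial lacks 90% power for yoga versus TAU. The document supports neither. The paired t-test at d = 0.5 gives 63 rather than 67, several between-arm calculations return about 67, and d = 0.5 is only the conventional reading of medium.

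It does not rescue the paragraph. Each between-arm route to 67 or to 90% needs something the article does not state: an effect of about 0.67, a correlation near 0.7, or an averaged contrast with a constant effect from month 1. If a two-group formula was used, the pre-versus-post label misdescribes it. That is a fault in what is written, not a detail left out.

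**Conclusion.** The point holds in a limited form. The only stated basis for 67 per arm is pre-versus-post comparison with an unquantified effect, so 90% power for the randomised comparison is not demonstrated.

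The size of any shortfall depends on two unstated things: what medium means, and which between-arm contrast is primary. On the plainest reading (d = 0.5 in SD-of-change units, one time point, no adjustment) power lies between 61% if 67 per arm are evaluable and 71% if all 80 are. Strong baseline correlation or averaging over visits would close the gap. A low correlation at a single visit would not. The calculation shows a claim without support for its main use; it does not prove an arithmetic error or an underpowered trial.

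**What to change.** Keep 160 patients and rewrite the first paragraph of section 2.2.1:

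- Replace the pre-versus-post basis with the between-arm contrast in change (group-by-time or baseline-adjusted) at a named time point. If an average over follow-ups is intended, say so.
- State the numeric effect size, whether it is in raw-score or change-score SD units, and any assumed correlation, with its source.
- Restate the power with 67 evaluable and 80 recruited per arm, or the difference detectable with 90% power. For an unadjusted single-visit comparison at alpha 0.01, the detectable d is about 0.67 and 0.62 respectively.

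The cost is one rewritten paragraph and no extra patients. The downside is that the stated power may be less favourable than 90%.

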### Plans for data storage, handling, and statistical analysis

2.4

Data storage and handling is under the supervision of a collaborator (biostatistician) from the Department of Biostatistics at NIMHANS. The data is coded and stored under password protection. Data analysis will also be carried out under the supervision of the Principal Investigator and the biostatistician. The person carrying out the analysis will be blind to subjects’ group allocation status. Intention to treat analysis and per protocol analysis would be done to account for the missing data. Interim analysis is planned at the end of 3 years of the study. There is no formal Data Monitoring Committee for the trial. However, a Trial Steering Committee is in place to monitor the conduct of the study. In addition, the Wellcome Trust - DBT India Alliance Expert Review committee reviews the trial annually and suggests modifications if needed. The NIMHANS Human Ethics Committee monitors ethical issues related to the trial.

Primary outcome measures: change in SAPS, SANS, BPRS scores and sub-scores; change in TRENDS accuracy scores (TRACS); change in serum BDNF; change in plasma oxytocin; and differences in BOLD response among study groups, and treatment effects (i.e., baseline vs follow-up comparison).

Secondary outcome measures: change in WHOQUOL-BREF scores; change in Perceived Stress Scale (PSS) scores; change in SOFS scores; change in serum cortisol; change in serum IGF-1; and change in gene expression of BDNF and oxytocin genes.

Physical activity levels of all subjects is obtained using a standard questionnaire and controlled for during analysis. Antipsychotic medication dosage would be recorded and analyzed as a covariate.

Data analysis will be done using SPSS Version 24 (IBM SPSS Statistics for Windows, Version 24.0. Armonk, NY: IBM Corp). Basic details of patients who opt out of the study are recorded, and measures to deal with dropouts, missing data, and non-adherence will be taken in collaboration with the biostatistician. Intent-to-Treat analysis will be done including data of all randomized subjects. Mixed model multivariate analysis will be used. Details of imaging analysis are given in the section on imaging below.

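### fMRI is listed among the primary parameters said to need at least 67 patients per arm, but imaging is planned in 50 per arm with no power given for that number

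*Protocol article*

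**What the plan says.** Section 2.2.1 (Sample size estimation) says that the calculation was made "for the assessment of primary parameters (SAPS, SANS, and BPRS scores, serum BDNF, Oxytocin, TRENDS fMRI". It cites earlier data "supporting a medium effect size for yoga-based intervention" and concludes that at least 67 patients per arm, for pre-versus-post comparisons, are "required to detect a two-tailed significant difference of" alpha "0.01 with an estimated 90% power". Recruitment is set at 80 per arm to cover drop-outs; no drop-out rate is stated.

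The next paragraph of the same section turns to imaging. "The subset sample size of 50 in each arm for imaging studies", described as pre and post scans in each group, is declared enough for a random-effects analysis of BOLD change with random-field family-wise correction. No effect size, power or detectable difference accompanies it.

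Imaging is primary throughout. Section 1.2.1 names "plasma oxytocin and functional magnetic resonance imaging (fMRI") in the second primary objective. Section 1.3.1 makes change in cerebral activation the third primary hypothesis. Section 2.4 lists "differences in BOLD response among study groups, and treatment effects (i.e., baseline vs follow-up comparison") among the primary outcomes. The imaging analysis text at the end of section 2.5 sets a voxel-wise analysis with family-wise correction at P < .05.

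**The concern.** Two adjacent paragraphs give different answers for one primary outcome. If fMRI belongs to the set that needs 67 per arm, 50 is 17 short (17/67 = 25%). If it does not belong there, the 90% power claim should not name it. Whether the last item in the list is read as one entry (TRENDS fMRI) or as two, fMRI is in it.

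The reason offered for 50 does not close the gap. That a random-effects model can be fitted and its false-positive rate controlled says nothing about the chance of detecting a real effect. At stake is how the imaging result is read: the 90% figure, as printed, appears to cover BOLD response, and the planned imaging sample does not deliver it on the protocol's own terms.

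**Working it through.** **Inputs.** From section 2.2.1: two-sided alpha 0.01, power 90%, at least 67 per arm, 80 recruited per arm, 50 per arm imaged, a pre-versus-post comparison, and a medium effect with no number attached.

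**Formulas (noncentral t).**
- Paired: power = 1 − F(t₀.₉₉₅; df = n − 1, noncentrality d√n).
- Two-sample, n per arm: power = 1 − F(t₀.₉₉₅; df = 2n − 2, noncentrality d√(n/2)).

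**Step 1: the protocol's 67.** Because no effect size is stated, d = 0.5 is an assumption here. The sizes needed per arm are:
- paired, normal approximation: (2.576 + 1.282)²/0.25 = 59.5, so 60;
- paired t: 63;
- signed-rank test with normal data (efficiency 3/π): 66;
- two-sample: 120 by normal approximation, 121 by t.

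None gives 67 exactly. The signed-rank version is close, but the protocol names no test. So 67 is not reproduced from d = 0.5, and it is safer to work back from it.

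**Step 2: effect implied by 67 per arm at 90% power, alpha 0.01.** Paired d = 0.483; two-sample d = 0.675.

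**Step 3: same effect, 50 per arm, alpha 0.01.**
- Paired: noncentrality 0.483 × √50 = 3.42, power 76.6%.
- Two-sample: noncentrality 0.675 × √25 = 3.375, power 77.1%.

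The fall is from 90% to about 77% on either reading. As a cross-check, the signed-rank version at d = 0.5 gives 90.6% at 67 and 77.5% at 50.

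**Step 4: if 50 counts baseline scans only.** Assume 67/80 as retention: 50 × 67/80 = 41.9, about 42 per arm. Power at the implied effect is 66.7% paired and 67.5% two-sample.

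**Step 5: effect detectable with 90% power at 50 per arm, alpha 0.01.** On a single summary value, before any voxel-wise correction: 0.565 SD paired, 0.785 SD between arms.

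**Step 6: sensitivity to alpha at 50 per arm.**

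| Per-test alpha | Paired, d = 0.5 | Two-sample, d = 0.5 | Two-sample, d = 0.675 |
|---|---|---|---|
| 0.05 | 93% | 70% | 92% |
| 0.01 | 80% | 45% | 77% |
| 0.001 | 52% | 20% | 50% |

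A voxel-wise analysis with family-wise correction is stricter than one test at 0.05. How much stricter cannot be worked out from the document; the 0.001 row is only an illustration.

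**The case against.** The best defence is that imaging has its own paragraph and its own error control, family-wise P < .05, so neither the 67 nor alpha 0.01 was meant to apply to it. On one test at 0.05, 50 patients give 93% paired power at d = 0.5. Part of this stands: the document sets no alpha of 0.01 for the imaging analysis, so 77% is what the sample-size statement implies at 50 per arm, not the actual power of the voxel-wise test. It does not remove the conflict, because the protocol itself puts fMRI in the list covered by 67, and the correction is stricter than a single test at 0.05.

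It can also be said that the mention of pre and post scans most naturally means 50 patients with both scans, drawn from 80 recruited. That is fair, and it makes the 42-per-arm figure conditional. Fifty completers is still fewer than 67.

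A reader might go further and infer that imaging power is only 45%, or 37% after losses. Those are two-sample figures at an assumed d = 0.5 and alpha 0.01. On the same assumptions 67 per arm gives only 61%, so most of the shortfall comes from sizing the trial on a pre-versus-post comparison, which is a separate matter from 50 versus 67. Nor is a 16% drop-out rate the trial's own figure: it is only 1 − 67/80.

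**Conclusion.** The inconsistency is real and rests on the text of one section. The protocol claims 90% power at 67 per arm for a set that includes fMRI, images 50 per arm, and gives no power for that number. On the protocol's own terms the cost is a fall from 90% to about 77% at alpha 0.01, or to about 67% if the 50 are baseline scans and 67/80 retention is assumed. These figures rest on the effect implied by 67 and on a single summary measure. The conflict between 67 and 50 does not depend on them.

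The true power for BOLD response cannot be determined, since no BOLD effect size is given. A reader might also infer that BOLD must be demoted to a secondary outcome; the documents do not require it, and doing so would mean rewriting the second primary objective and the third primary hypothesis. How a null imaging result would be interpreted is not stated, so misreading it is a risk rather than a demonstrated fault. The clinical and laboratory outcomes are not touched by this point.

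**What to change.** In section 2.2.1:

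1. Remove fMRI from the parameters covered by the 67-per-arm, 90%-power statement.
2. Replace the claim that 50 per arm is enough with the power or detectable effect that 50 per arm gives for a pre-specified BOLD summary, stating the alpha and assumptions. For example: at alpha 0.01 and 90% power, on a single summary before voxel-wise correction, about 0.56 SD paired or 0.78 SD between arms. If another alpha is intended for that summary, recompute on it; do not present these values as describing the voxel-wise P < .05 analysis.
3. Say whether 50 means scanned at baseline or with both scans.

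The cost is a change of wording, dated because the trial is already under way, and a less favourable stated power for imaging. No extra scans or patients are needed, and BOLD response can stay a primary outcome.
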